### Participant timeline

Following the opening of screening in January, patients can enter the study at any time; they will go through a pre-screening period until they are randomized in September. We have chosen a common fixed period for inclusion to avoid confounding seasonality factors. During the pre-screening period, trial outcomes are collected but no treatment is given. Enrollment is preceded by a pre-screening period of 9 months to identify patients with inclusion criteria, and exclude, before randomization, any participants who are unlikely to be adherent. A patient will be in the trial for 2 years post-randomization (i.e., until September 2019 for those entering in September 2017). After the inclusion visit, visits will occur every 3 months over 2 years. Furthermore, each patient will complete the self-administered questionnaires including the PO-SCORAD at home through an application on their computer or phone, or otherwise on paper, every 4 weeks. The time schedule of enrolment and visits is provided in Table 1 and Fig. 1.

**Table 1 Tab1:** Time schedule of enrolment and visits

Actions	Visit 0 Screening	Visit 1 Inclusion	Visits 2–8 Follow-up	Visit 9 End of trial
Written informed consent	X			
Web-based randomization		X		
Demographic details	X	X		
Medical history	X	X	X	X
Physical examination	X	X	X	X
Investigator Global Assessment	X	X	X	X
Eczema Area and Severity Index, Severity of Atopic Dermatitis Index		X	X	X
Quality of Life: Dermatology Life Quality Index		X	X	X
Patient-Oriented Severity of Atopic Dermatitis Index, Patient-Oriented Eczema Measure	X	X	Computer record every 4 weeks	X
Estimation of solar exposure		X	X	X
Complete blood count, serum chemistry, serum creatinine, serum calcium and phosphate, serum parathyroid level	X			X
Serum total IgE level		X	X	X
Vitamin D dosage		X	X	X
Delivery of oral vitamin D or placebo vial		X	X	
Checking for adverse events			X	X

**Fig. 1 Fig1:**
[figure not shown]
Overview of the study

### Assignment of interventions

#### Sequence generation and allocation concealment mechanism

Participants who meet the eligibility criteria and have signed informed consent will then be randomly assigned, in a 1:1 ratio, to either vitamin D or placebo, and within each arm to either the sequence UV–observation or the sequence observation–UV through an automated web-based system. A permuted block randomization scheme will be used, with stratification according to the clinical site, age (three age groups) and disease severity (two groups: moderate or severe). The list will be balanced by blocks of random size in order to ensure total unpredictability. Randomization can occur on the day of inclusion (Visit 1).

Since we offer phototherapy sessions exclusively during winter periods, the carry-over effect is not a concern in our study (Fig. 2).

**Fig. 2 Fig2:**
[figure not shown]
Figure SPIRIT

#### Blinding

This study is conducted as open-label regarding phototherapy, since blinding cannot be implemented, but it is double-blind for vitamin D therapy.

Vitamin D: patients, investigators and outcome assessors will be blinded. Although it would have been possible to implement logistics with a blinded switch to placebo for patients reaching normal vitamin D levels, the absence of supplementation dose adaptation based on vitamin D serum level will help maintain the blinding.

Phototherapy: patients and investigators will not be blinded, and cannot be. We will address the problem of blinding with regard to phototherapy by masking the allocated treatment (phototherapy or observation) for the investigator in charge of scoring disease severity. However, some objective clues (e.g., tanning, if present) cannot be masked.

### Data collection, management, and analysis

#### Data collection methods

Table 1 shows data collection at inclusion and at follow-up visits.

#### Data management

All information required by the study protocol is to be recorded in the case report forms and an explanation is to be provided for any missing data. Data is to be collected progressively, as obtained, and recorded explicitly in the case report forms.

An electronic case report form (e-CRF) will be made available and data capture will be carried out in the centers using a web interface (Clinsight software, Ennov, Paris, France). Only an Internet connection and a browser are required. A document on how to use this tool will be provided for the investigators. The interface between the clinical research associate and the investigator will thus be provided, also making remote data collection and control possible. Data consistency tests will be incorporated in electronic format. An audit function is incorporated in the e-CRF, thus making it possible to follow any change in study data. This function also makes it possible to clearly identify the person who has made a change, with the date; comments can be added.

If requested, a hard copy will be printed at the end of the study, authenticated (dated and signed) by the investigator, and copies will be sent to the sponsor and archived.

The procedures applied are those used Rennes CHU and comply with Good Clinical Practice and the legal and regulatory requirements in force.

#### Statistical methods

The statistical issue for the primary outcomes is the analysis of repeat measures (up to 12 measures for each 1-year period, on the PO-SCORAD, a self-administered questionnaire the results of which are collected through an application on computer or phone, at home) applied to a crossover design (two 1-year periods, two sequences). When repeat measures are analyzed, there are many possible hypotheses that could be of interest. We focused on a main effect hypothesis test for the effect of a single predictor variable (treatment: phototherapy) averaged across all other factors, and the sample size calculation was designed accordingly. We are interested in the usual factors, namely ‘Treatment’ (phototherapy/no phototherapy) and ‘Time’. However, the nature of the design (crossover trial) needs to be taken into account. This means that we need to consider the following factors: ‘Period’ – first winter/second winter, ‘Order’ – phototherapy–no phototherapy or no phototherapy–phototherapy, and ‘Carry-over’. It was anticipated that vitamin D could act as a quantitative effect-modifier on phototherapy. We therefore decided to include an interaction term in the analysis. We will use a single model with the following main effects: Treatment-1 (phototherapy/no phototherapy), and Treatment-2 (vitamin D/placebo), Period, Order, and Carry-over terms as well as an interaction term between Treatment-2 and Treatment-1. As an interaction of Time and Treatment could occur, we plan to add an interaction term to the model. The other primary outcome, the cumulate consumption of TAT (number of tubes) during the winter, is a quantitative variable. It will be analyzed using a mixed model with the following main effects: Treatment-1 (phototherapy/no phototherapy), and Treatment-2 (vitamin D/placebo), Period, Order, and Carry-over terms as well as an interaction term between Treatment-2 and Treatment-1. As this outcome is a summary of winter consumption, no interaction of Time and Treatment will be added to this model. Adjustment will be made on the variables used in the allocation process (region – north vs. south), age as a continuous variable, and disease severity (moderate vs. severe).

For descriptive purposes, it is instructive to carry out an analysis based on a summary of the statistics (a quantity calculated from each curve), which can reflect important aspects of the problem at hand – we have chosen the area under the curve (AUC) and the mean amplitude of PO-SCORAD score ranges. Descriptive statistics (mean and standard deviation) of the PO-SCORAD for each visit will also be provided. Normal distribution is assumed in the modeling analysis for the primary outcomes (PO-SCORAD severity score over two 1-year periods; cumulate consumption of TAT during winter) and will be checked at this stage.

The main analysis will be based on the adjusted model and will follow the ‘intention to treat’ principle, namely all participants, as randomized, will be analyzed; outcome data obtained from all participants, regardless of protocol adherence, will be used. Mixed model techniques (PROC MIXED) will be applied.

The multiplicity adjustment strategy used is a hierarchical closed test procedure, where the primary endpoints are ordered as follows: (E1) repeat measures of the PO-SCORAD severity score over 1 year and (E2) cumulate consumption of TAT over winter. We will test E1 and E2 sequentially at the same two-sided level of 0.05; we will test E1 first, if it proves significant, will we test E2. A Wald test with Kenward–Roger degrees of freedom will be used.

No subgroup analyses nor interim analyses are planned.

For secondary analyses, we will use up to four measures per 1-year period, collected at each clinical visit (every 3 months), including investigator-based severity scores (Eczema Area and Severity Index, Severity of Atopic Dermatitis Index, Investigator Global Assessment), patient-reported severity and quality of life scores (Patient-Oriented Eczema Measure, Dermatology Life Quality Index), serum vitamin D levels, total IgE serum levels, weeks of satisfactory control, inter-visit cumulate consumption of TAT, and synthetic patient-reported satisfaction at the end of each winter.

All analyses will use procedures available in SAS software 9.4 (SAS Institute, Carry, NC, USA).

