### Trial design

The study is a pragmatic, multicenter, national, randomized (1:1), superiority, crossover (two periods, two sequences) trial lasting 2 years (including two successive winters), and exploring add-on phototherapy versus observation in subjects receiving standard care (i.e., TAT). In the same population, we will be testing the LTC provided by oral supplementation of vitamin D versus placebo in a randomized, superiority, double-blind, parallel-group trial. Pragmatic trials [29] are the best-suited designs for studying add-on therapies in the context of long-term AD disease. The main pragmatic options are the following: recruitment in a primary care population, standard vitamin D supplementation, regimen not adapted to serum levels, strictly ‘as usual’ TAT use, and no recommendation on changes in lifestyle.

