On the basis of the sample size simulation (Additional file 1), we chose a total sample size of 340 subjects. This calculation was performed on the basis of a parallel-arm design; thus, using a crossover design, we considered we could halve the sample size. The assumption of no carry-over effect is allowed when planning a sample size for a crossover trial. For an intervention only in winter, we considered carryover would be minimized by design. Using a uniform and balanced crossover design, the treatment difference will not be aliased with sequence or period effects. However, an interaction of time and treatment should be taken into account, as we anticipate this could occur.

Power considerations in the area of repeat measures, crossover design and interaction between time and treatment are not straightforward. We therefore used GLIMMPSE, as for a two-arm trial. We realize that halving the sample size could appear simplistic and we therefore compared the sample size calculations between (1) a two parallel arm trial and (2) a crossover trial, considering only the last measure as the outcome, to check that the sample size reduction was not too optimistic. Finally, anticipating that 10–15% of patients will not complete the entire study (two 1-year sequences), the planned number of subjects to be enrolled is set at 200.

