Since both phototherapy and vitamin D supplementation are good candidates for LTC of AD disease activity, our proposal is to study these two treatments jointly. We will therefore use a factorial design to assess the effects of phototherapy and vitamin D supplementation on LTC within the same study; since solar exposure (and to a lesser extent artificial UV exposure under phototherapy) favors vitamin D synthesis, this design has the potential to explore the interaction between phototherapy and vitamin D supplementation in disease control and serum vitamin D levels in winter and all-year round. We have chosen a crossover design for phototherapy to adjust on personal characteristics (phototherapy and sensitivity to UV exposure being major determinants of phototherapy efficacy) [32–34]. We chose a fixed and common period for inclusion to avoid confounding by seasonality. While patients will be able to sign their written consent at any time in the pre-screening period, they will be randomized in September and we cannot exclude that some patients may drop out of the study before the randomization. The alternative would be to randomize patients throughout the year and to take into account seasonal effects, but the approach to measure this would have been complex in a study with pragmatic options and long-termfollow-up. Since we provide phototherapy sessions exclusively during winter periods, a carry-over effect is not a concern in our study.

Our trial provides the possibility of reducing topical anti­inflammatory treatment use. Further evaluation will be needed if the exploratory trial on phototherapy opens up new avenues (novel phototherapy, pro-active strategy).

As we are conducting a long-term study, we plan the following procedures to minimize attrition bias: firstly, any participant who is recommended systemic immunosuppressants will discontinue the study; secondly, our trial includes strong pragmatic options [29, 34–36] such as primary care population, standard vitamin D supplementation that is not adapted to serum levels, ‘as usual’ TAT use, and no recommendations for changes in lifestyle; thirdly, the trial includes logistic support to ensure adherence such as trained study nurses in the field facilitating participant adherence; and, finally, it will test new maintenance therapies superimposed on usual care. It can be noted that ‘add-on’ therapy trials on asthma have better rates of adherence [37].

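### Both primary models fit Order and Carry-over alongside Treatment-1 and Period in a two-period, two-sequence crossover, so the averaged phototherapy effect is not estimable as written

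*Protocol article*

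**What the plan says.** The Trial design section describes the phototherapy comparison as a "randomized (1:1), superiority, crossover (two periods, two sequences) trial lasting 2 years".

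The Statistical methods section defines Order as the sequence group and names Carry-over next to it: "phototherapy–no phototherapy or no phototherapy–phototherapy, and ‘Carry-over". For PO-SCORAD (E1), it then specifies a single model with main effects for Treatment-1 (phototherapy) and Treatment-2 (vitamin D), plus "Period, Order, and Carry-over terms as well as an interaction term between Treatment-2 and Treatment-1", and a further Time-by-Treatment interaction. The same list is repeated for winter TAT consumption (E2), with one difference: "As this outcome is a summary of winter consumption, no interaction of Time and Treatment will be added to this model". On multiplicity: "We will test E1 and E2 sequentially at the same two-sided level of 0.05", with E2 tested only if E1 is significant.

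Elsewhere carry-over is treated as absent. The Sample size section says "The assumption of no carry-over effect is allowed when planning a sample size for a crossover trial", halves a parallel-arm total of 340, and states that a uniform, balanced crossover keeps the treatment difference free of aliasing with sequence or period. The section on sequence generation says "the carry-over effect is not a concern in our study", and the Discussion repeats that "a carry-over effect is not a concern in our study".

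**The concern.** A two-period, two-sequence crossover has only four sequence-by-period means. Intercept, Treatment-1, Period and Order use all four, which leaves nothing from which to estimate a separate Carry-over term. If all are fitted, the phototherapy contrast is not identified.

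The article describes phototherapy as the predictor on which the sample size and the main-effect test are built. If its contrast is undefined, the analyst has to remove a term to obtain a result, and the possible removals answer different questions with different precision. That choice should not be left until data are available, least of all on E1, which gates E2.

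**Working it through.** **1. The plan's own figure.** Inputs from the Sample size section: 340 for a parallel-arm trial, halved for the crossover, 10–15% non-completion, 200 enrolled.
- 340 / 2 = 170.
- 170 / (1 − 0.15) = 200; 170 / (1 − 0.10) = 188.9, i.e. 189.

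So 200 is reproduced with 15% loss. The 340 itself cannot be rebuilt, because the means per time point are in an additional file that is not shown.

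**2. The alias.** Use 0/1 coding: Order = 1 for the UV–observation sequence, Period = 1 for year 2, Carry-over = 1 in the year after phototherapy.

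| Sequence | Year | Treatment-1 | Period | Order | Carry-over | Period + Order − Treatment-1 − 2 × Carry-over |
|---|---|---|---|---|---|---|
| UV–observation | 1 | 1 | 0 | 1 | 0 | 0 + 1 − 1 − 0 = 0 |
| UV–observation | 2 | 0 | 1 | 1 | 1 | 1 + 1 − 0 − 2 = 0 |
| observation–UV | 1 | 0 | 0 | 0 | 0 | 0 |
| observation–UV | 2 | 1 | 1 | 0 | 0 | 1 + 0 − 1 − 0 = 0 |

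The relation is zero in every cell, so one of the four terms is redundant. With other codings the coefficients change, but the redundancy does not.

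**3. Rank of the stated models.**
- E2 (vitamin D × sequence × year, 8 cells; intercept, Treatment-1, Treatment-2, Period, Order, Carry-over, interaction): 7 columns, rank 6. The phototherapy contrast averaged over vitamin D is not estimable. The vitamin D contrast and the Treatment-1 × Treatment-2 interaction are.
- E1 (the same cells × 12 times, with Time and Time × Treatment-1, and Treatment-1 constant within each year): 7 + 11 + 11 = 29 columns, rank 28. The time-averaged phototherapy effect is not estimable.
- Removing either Carry-over or Order restores full rank in both models. Adding columns (region, age, severity) cannot remove a dependence among columns already there.

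**4. What each removal yields.** Let s² be the variance of a patient's yearly summary, r the correlation between years, and n the number of patients in equal sequences.
- *Carry-over removed, Order kept:* within-patient estimate, variance 2s²(1 − r)/n. At n = 170 and r = 0 this is 2s²/170 = 4s²/340, the variance of the 340-patient parallel trial. Planned power is therefore kept at r = 0 and exceeded at r > 0. If 340 gave 80%, an assumed r of 0.5 gives about 98%.
- *Order removed, Carry-over kept:* the generalised least squares weights for Treatment-1 are +1 and −1 on the two year-1 means and 0 on both year-2 means. This is a first-year between-patient comparison with variance 4s²/n, which is 2/(1 − r) times larger: 2-fold at r = 0, 4-fold at r = 0.5.

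**5. E1 power in the second case.** Power = Φ((1.960 + z) × √(n/340) − 1.960), where z is the normal quantile of the power that 340 is assumed to give. The 10–15% loss refers to the whole two years, so year 1 would hold between 170 and 200 patients.

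| Power assumed at 340 | n = 170 | n = 200 |
|---|---|---|
| 80% (2.802) | Φ(1.981 − 1.960) = 50.8% | Φ(2.149 − 1.960) = 57.5% |
| 90% (3.242) | Φ(2.292 − 1.960) = 63.0% | Φ(2.486 − 1.960) = 70.1% |

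The article states no power for E2, so none is computed.

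**The case against.** **A first-year-only fallback is not what the text prescribes.** A reader might infer that the trial is headed for about 51% power. The documents do not support that. Nothing proposes dropping Order and keeping Carry-over, and the repeated dismissal of carry-over points towards dropping Carry-over, which gives the planned within-patient analysis. If the software zeroes Carry-over as the redundant column, the printed coefficient may also be the within-patient one. This stands: the low power is conditional on one resolution. It does not rescue the stated model, because the answer then rests on an unstated parameterisation.

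**The E1 alias depends on coding.** Phototherapy runs from October to March, while PO-SCORAD is collected every 4 weeks all year. If Treatment-1 were coded as on only in treated winter months (checked with six of 12 times on and no Time × Treatment term), the model has 18 columns, rank 18, and Treatment-1 is estimable. Full rank also returns if untreated baseline scores are modelled as responses. Both are true, but the article describes two 1-year periods compared on an averaged phototherapy effect and states neither device. E2 has one value per winter, so this escape is not available there.

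**Phototherapy is called exploratory.** The Background labels vitamin D the main trial, and the vitamin D contrast is intact. That limits the scope, but the sample size and the stated main-effect test are for phototherapy.

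**Assuming no carry-over for planning does not forbid examining it later.** Correct. It can be examined separately, but not in the primary model together with Order.

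**The analysis plan may settle it.** The point is not missing detail: the model is written out for both outcomes, and the list as written is over-specified.

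**The power figures ignore covariate adjustment.** Adjustment for severity, age and region may reduce between-patient variance and raise the first-year figures somewhat. The article gives nothing from which to size this.

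**Conclusion.** The point holds in a bounded form. As written, both primary models contain a redundant term and the averaged phototherapy effect is not estimable. For E2 this is exact and needs no numerical assumption. For E1 it rests on Treatment-1 being constant within each 1-year period. Vitamin D and its interaction with phototherapy are not affected.

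The consequence is an undetermined primary analysis rather than a certain loss of power. One resolution retains at least the planned power. The other gives E1 about 51–57% with 170–200 patients, taking the stated minimum of 80% at 340 as exact, or 63–70% if 340 gave 90%, before any gain from covariates. The protocol's claim that treatment is not aliased with sequence or period is correct only without the Carry-over term, so the stated model is also at odds with the assumption behind halving 340 to 170.

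**What to change.** Delete Carry-over from both primary models. Keep Treatment-1, Treatment-2, their interaction, Period and Order, with a patient effect and the stated covariates; for E1 also keep Time and Time × Treatment. State that carry-over is assumed negligible, as the Sample size, sequence generation and Discussion sections already do. If reassurance is wanted, prespecify a first-year-only comparison as a sensitivity analysis, noting its lower power.

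The cost is a wording change made before unblinding of vitamin D and before any phototherapy comparison is run; design, enrolment and data collection are untouched. The small downside is that the primary phototherapy estimate then relies on negligible carry-over from the first winter to the second year.

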### Participants and eligibility criteria

#### Inclusion criteria

Eligibility criteria: patients with AD (Hanifin and Rajka criteria), aged 15 or over, with > 2 years of disease evolution, moderate-to-severe disease (Investigator Global Assessment > 2), seasonality in disease severity (improvement in summer), and fewer than 100 previous phototherapy sessions in their lifetime. Eligible patients are to have received TAT for at least 12 weeks and to have symptoms requiring an intensification of the therapy, and they are to have easy access to a phototherapy cabin (widely available in primary care dermatology private practices in France).

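### The model for winter TAT tubes omits pre-randomisation TAT use, so the vitamin D comparison on that outcome probably gives up some precision, by an amount the protocol does not let one fix

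*Protocol article*

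**What the plan says.** In Statistical methods, E2 is described on its own: "The other primary outcome, the cumulate consumption of TAT (number of tubes) during the winter, is a quantitative variable". The model follows: "It will be analyzed using a mixed model with the following main effects: Treatment-1 (phototherapy/no phototherapy), and Treatment-2 (vitamin D/placebo), Period, Order, and Carry-over terms", together with the interaction between the two treatments. The adjustment set is then named: "Adjustment will be made on the variables used in the allocation process (region – north vs. south), age as a continuous variable, and disease severity" in two levels. The same section states that "The main analysis will be based on the adjusted model". The covariates are therefore fixed in the text, and earlier TAT use is not among them.

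Three other statements bear on whether such a covariate could be built:

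- Participant timeline: "Enrollment is preceded by a pre-screening period of 9 months", and "During the pre-screening period, trial outcomes are collected but no treatment is given". Patients may enter at any time from January and are randomised in September.
- Inclusion criteria: "Eligible patients are to have received TAT for at least 12 weeks".
- Trial design: TAT use is left as usual, and vitamin D against placebo is a parallel-group comparison. The Background calls vitamin D the main trial.

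**The concern.** How many tubes a patient uses over a winter plausibly depends on personal habit, the body area affected and the prescriber. A moderate/severe split is a coarse stand-in for these. In the crossover each patient is their own control, so this variation largely drops out of the phototherapy contrast. It does not drop out of the vitamin D contrast, which is wholly between patients.

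The vitamin D comparison also has the least precision to spare. The sample size was worked out for phototherapy on PO-SCORAD and then halved because of the crossover, a saving that a parallel-group comparison does not receive. The Discussion holds that add-on trials need both severity and TAT consumption, so a wider interval than necessary on E2 touches one of the two outcomes on which long-term control is judged.

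**Working it through.** **The plan's own figure.** From Sample size: 340 for a parallel design, halved to 170 for the crossover, with 10–15% dropout. 170/(1 − 0.15) = 200, the stated enrolment; at 10% it is 170/0.90 = 188.9, so 189. The stated 200 is reproduced at 15%, and the present point does not alter it. It leaves about 85 (completers) to 100 (enrolled) patients per vitamin D arm.

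**Inputs the document does not give.** No standard deviation, effect size or correlation is stated for tubes. Assumed:

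- rho, the partial correlation of the pre-randomisation TAT rate with each winter's tubes, after region, age and severity: 0.2 to 0.5.
- r, the correlation between the two winters' tubes: 0.6, borrowed from the base correlation used for PO-SCORAD.
- An unadjusted power of 80% for vitamin D on E2, as a reference only; the plan states no power for this comparison.

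**Formulas.** The vitamin D contrast rests on each patient's mean over two winters. In units of the one-winter variance, that mean has variance (1 + r)/2, and its covariance with the standardised baseline is rho. Hence

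variance ratio (adjusted/unadjusted) = 1 − 2·rho²/(1 + r).

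Using one winter only, it is 1 − rho². Power after adjustment is Φ(2.80/√ratio − 1.96), where 2.80 = 0.84 + 1.96.

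**Every patient has a usable baseline:**

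| rho | variance cut, one winter | variance cut, two winters (r = 0.6) | power from 80% |
|---|---|---|---|
| 0.2 | 4% | 5% | 81.6–82.0% |
| 0.3 | 9% | 11% | 83.6–84.5% |
| 0.4 | 16% | 20% | 86.4–87.9% |
| 0.5 | 25% | 31% | 89.9–92.2% |

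Example at rho = 0.4, two winters: 1 − 2(0.16)/1.6 = 0.80; 2.80/√0.80 = 3.13; 3.13 − 1.96 = 1.17; Φ(1.17) = 88%.

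**Only a share has one.** Patients with an imputed mean contribute no reduction, so the cut shrinks roughly in proportion. With 70% usable (an illustration, not a figure from the protocol):

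- rho = 0.2: cut 2.8–3.5%, power 81.1–81.4%.
- rho = 0.3: cut 6.3–7.9%, power 82.5–83.1%.
- rho = 0.4: cut 11.2–14.0%, power 84.4–85.6%.

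**Check by simulation** (170 patients, r = 0.6, everyone with a baseline). For vitamin D the variance ratio was 0.90 at rho = 0.3 and 0.71 at rho = 0.5, against 0.89 and 0.69 from the formula. For the within-patient phototherapy contrast it was 1.01 in both cases, so no gain.

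**The case against.** **The covariate is not shown to exist.** Its availability rests on one general sentence about the pre-screening period. Table 1 has EASI, SCORAD, DLQI, IgE and vitamin D starting only at Visit 1, so that sentence cannot cover every outcome. This stands, and it makes the point conditional. It does not show the data are absent: Table 1 has no TAT row at any visit, including those at which tubes must be counted. The 12-week criterion shows prior exposure, not that tubes were recorded.

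**If it exists, it is uneven.** Windows run from about nine months to almost none. In the first season, ethics approval (18/08/15) and first inclusion (30 September 2015) are about six weeks apart. The window lies largely outside winter, in patients selected for improving in summer. This stands too: rho may be modest, and some patients will have no usable value.

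**E2 is gated and the sample size targets phototherapy.** E2 is tested only if E1 is significant, so the power figures are conditional. The single-predictor hypothesis behind the sample size is phototherapy, which gains nothing here. Both are correct and limit the scope.

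**The choice is valid as it stands.** Randomisation is stratified by site, age and severity, which partly balances prescribing habit, and adjusting for allocation variables is coherent. A reader might infer that chance imbalance in habitual TAT use biases the vitamin D estimate or inflates its type I error. It does neither: the confidence interval and test already allow for chance imbalance.

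**It could be left to the analysis plan.** The article does not leave it open: it names the model terms, the adjustment set and the adjusted model as the main analysis.

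**Conclusion.** The point holds as a limited, conditional one. The stated E2 model leaves out a covariate that the protocol suggests was collected, and the between-patient vitamin D comparison on E2 probably loses some precision as a result.

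The size cannot be derived from the document. It depends on assumed values of rho and r, and on the share of patients with a usable baseline. A gain of 1 to 2 power points at rho = 0.2, or of 4 to 8 at rho = 0.4, from a reference of 80% and given a significant E1, is a fair summary; the ranges run from 70% to all patients having a baseline. A reader might take the rho = 0.5 row, with 10 to 12 points, as the expected gain. The documents do not support that: no correlation for tubes is given, that row assumes a baseline for everyone, and the season and length of the window argue for something lower. Nor do they support describing the precision as certainly available, since no pre-randomisation tube count is defined.

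**What to change.** Before unblinding:

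1. Confirm that TAT use was recorded before randomisation, and for how many patients. If it was not, the point lapses.
2. If it was, add the pre-randomisation TAT rate (tubes per 4 weeks over the patient's own pre-screening interval) as a fixed covariate in the E2 mixed model, alongside region, age and severity. Use one value per patient for both winters; a second-year baseline could have been affected by treatment.
3. Define what counts as a usable interval. For patients without one, use the pooled mean plus a missing-baseline indicator. This is valid because the value precedes randomisation.

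Cost: a short addition to the analysis plan and two degrees of freedom, with no extra visits, patients or change in sample size. The unequal length and season of the baseline may keep the gain small but cannot bias the randomised comparison.
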